### Trial design

This is an adaptive, two-stage randomised phase IIa, single-centre clinical trial that will aim to recruit 30 patients with severe Graves’ disease from secondary care at the Newcastle upon Tyne Hospitals NHS Foundation Trust. It is a single-blinded trial in which participants will be blind to allocation. Recruitment start date: October 2021; planned end of trial (last patient last visit): April 2024.

Stage 1 is a dose–response study using four doses of daratumumab (9 mg/kg, 3 mg/kg, 1 mg/kg, 0.5 mg/kg) and a colourless, volume-matched placebo infusion in approximately 15 patients (ie, five groups of n=3, randomised in a 1:1:1:1:1 ratio using permuted random blocks without stratification) (figure 1).

**Figure 1 F1:**
[figure not shown]
Design of the study. TRAb, thyroid-stimulating hormone receptor antibodies.

Following stage 1, an interim analysis will be performed of the first 15 patients in order to select an optimal dose(s) of daratumumab for stage 2. The dose selection will be based on an analysis of the reduction in TRAb concentration and safety assessed at 12 weeks. In stage 2, the remaining 15 patients will be randomised between placebo and one or two chosen doses of daratumumab depending on results of the interim analysis. Patients in both stages of the study will have all the same assessments and will be followed up for 24 weeks, with the primary endpoint being measured at week 12.

### Inclusion criteria

Patients ≥18 years old.Recent-onset Graves’ disease (within 12 months) (defined as date of first thyroid function test showing hyperthyroidism (FT4 and TSH) in current episode).TRAb concentrations above 10 U/L (on Roche or Brahms TRAb-binding assays).One or more of:Pretreatment severe hyperthyroidism (FT4 ≥50 pmol/L or FT3 ≥15 pmol/L).Persisting hyperthyroidism despite more than 12 weeks of antithyroid drug therapy (defined as FT3 above the upper limit of the reference range following 12 weeks of carbimazole treatment at a dose of 40 mg or more daily (or equivalent dose of propylthiouracil)).Inflammatory thyroid eye disease (defined as Clinical Activity Score ≥3) or thyroid dermopathy.Large (visible) goitre (WHO grade III).Two or more relapses (three episodes in total) despite completing 12 months or more of medical treatment on each occasion. Relapse is defined as FT3 above the upper limit of the local reference range.For women of childbearing potential, willing to use a highly effective contraceptive method during their participation in the trial.Able to understand and speak sufficient English to complete trial procedures.Willing and able to provide informed consent prior to any trial procedures taking place.

### Exclusion criteria

Previous thyroidectomy or radioiodine treatment within 2 years.Pregnant or breastfeeding, or with a plan for pregnancy within 6 months.Previous shingles, known untreated cervical dysplasia, hepatitis B and C or HIV infection.Anaemia (haemoglobin ≤100 g/L), thrombocytopenia (≤75×10^9^/L) or neutropenia (≤1.0×10^9^/L).Known chronic obstructive pulmonary disease (defined as a forced expiratory volume in 1 s <60% of predicted normal), persistent asthma or a history of asthma within the last 2 years (intermittent asthma without hospitalisation is allowed).Any significant physical or mental health condition that impacts the safety of the intervention, the interpretation of thyroid function or the ability of a participant to attend for intervention and safety monitoring, for example, major cardiorespiratory disease, renal or hepatic failure, pancreatitis, cancer undergoing active treatment (excluding non-melanoma skin cancer), untreated chronic infection including tuberculosis, psychosis and depression impairing activities of daily living.Current use of immunosuppressive therapy for TED or other conditions (within 3 months).Current or previous participation in a Clinical Trial of Investigational Medicinal Products research study within 4 months.Hypersensitivity or anaphylactic reaction to previous monoclonal antibody treatments or methylprednisolone.Inability, in the opinion of the investigator, to be able to complete the clinical trial visits or procedures.

### Risk assessment

Daratumumab is a licensed product for patients with myeloma and the main risk is that it will have a different side effect profile in patients with benign disease. The typical risks of daratumumab when used for myeloma include transient infusion reactions and haematological dyscrasias, the latter being accounted for by the bone marrow suppression in patients with myeloma and leading to a small risk of infection (≤5%).

Daratumumab interferes with urgent blood cross-matching and all patients will have a Coombs test and blood group and transfusion antibody screen prior to administration of daratumumab, as well as receiving an information card in case blood transfusion is needed. There is a potential for reactivation of latent viral illness, and so all participants will be screened for hepatitis B, C and HIV infection, and participants with previous shingles or current untreated cervical dysplasia will be excluded. There are no specific risks demonstrated in the Graves’ disease population who will be younger and in better overall health than the patient group who currently receive daratumumab for myeloma.

Participants will be offered a course of SARS-CoV-2 vaccination prior to treatment with investigational medicinal product (IMP). If loss of immunity to specific pathogens is detected at the end of the study, the participants may be offered repeat vaccination for tetanus, pneumococcus and SARS-CoV-2, where clinically appropriate. Throughout their participation in the study, patients will continue their regular ‘background’ medication for treatment of thyrotoxicosis (ie, antithyroid drugs, with or without levothyroxine) as prescribed by their clinician as per usual clinical care and will be carefully monitored with regular blood tests throughout the study.

### Patient identification, consent and screening

Potential participants with severe Graves’ disease within secondary care will be identified and approached in person, by post or email with a trial participant information sheet (PIS) by one of the clinical team members responsible for their usual management. Potential participants will also be identified and referred by local secondary care Patient Identification Centre sites, or can self-refer to the trial via adverts through organisations such as the British Thyroid Foundation (BTF). Consent discussions and written informed consent will take place in person at a research-specific clinic appointment, with the principal investigator or alternative member of the research team who is medically qualified and appropriately trained. For women of childbearing potential, consent discussions will include the need to use a highly effective form of contraception (as listed on the PIS) for the duration of their participation in the trial. Consent discussions will be documented in medical notes.

Following written informed consent, eligibility for the trial will be assessed by:

Demographics and medical history including medication history.Full external medical examination, including weight, heart (including resting pulse rate and 12-lead ECG), chest, abdomen, goitre size assessment, skin, eyes and neurological examination.Blood tests (full blood count (FBC), urea and electrolytes, liver function test (LFT), hepatitis B surface antigen, hepatitis C virus antibodies, HIV, bone chemistry, TRAbs, serum FT4, FT3, TSH, serum IgGAM, Coombs, blood group and red cell phenotyping).A urine sample pregnancy test for all female participants of childbearing potential (to be repeated where there is >14 days between screening and baseline visits).

The trial screening log will include reasons for screen fails and any reasons given for declining the trial.

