### Intervention

Each participant will receive two infusions, on day 0 and day 14 (±3 days). The prescribed daratumumab dose will be prepared in a 500 or 1000 mL bag of sodium chloride 0.9%, using the most recent available participant weight to calculate banded dose (see table 2 for volume and infusion rate). Each participant will be prescribed the same banded dose for both infusions, using the same weight for both. Where placebo is allocated, a volume-matched bag of sodium chloride 0.9% will be used. All participants will be pre-medicated with three non-IMPs, paracetamol (1 g orally), methylprednisolone (100 mg intravenously) and chlorphenamine (10 mg intravenously) at least 30 min prior to their allocated infusion.

**Table 2 T2:** Infusion rate table

Time (hour:min)	Rate (mL/hour)	Total volume at end of time (mL)
Stage 1 (1000 mL)		
1	80	80
2	160	240
3	240	480
4	320	800
4:40	320	1000
Stage 2 rate A (1000 mL)		
1	50	50
2	100	150
3	150	300
4	200	500
5	200	700
6	200	900
6:30	200	1000
Stage 2 rate B (500 mL)		
1	50	50
2	100	150
3	150	300
4	200	500

The maximum infusion rate of daratumumab was determined by the recommendation of the SmPC for daratumumab (DARZALEX 20 mg/mL concentrate for solution for infusion). For stage 1, all participants will receive the IMP/placebo diluted in 1000 mL sodium chloride 0.9% for both infusions. For stage 2, some patients may receive higher doses of daratumumab, so a more prolonged first infusion will be given to all participants. If participants have no IRRs during their first dose in stage 2, then the second dose may be given in 500 mL sodium chloride 0.9% with a faster infusion rate, in line with SmPC recommendations.

IMP, investigational medicinal product; IRRs, infusion-related reactions; SmPC, Summary of Product Characteristics.

Vital signs (pulse rate, blood pressure and temperature) will be recorded prior to the start of each infusion and every 15 min during the course of the infusion, and for 1 hour afterwards. Infusion-related reactions will be addressed as shown in table 3, and documented as an AE. Infusion charts will be completed to document compliance with prescribed dose. Participants will be followed up by phone approximately 2 days after each infusion visit to check for any AEs. After the day 14 visit, no further IMP will be administered. Patients will continue their regular medications, including antithyroid drugs and beta-blockers throughout the study, as deemed appropriate by the clinical team.

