### Assessments

Follow-up visits will take place at weeks 4, 6, 12 and 24 (±1 week); the details of assessments are provided in table 4. At each visit, concomitant medications will be recorded, an AE check will be performed, compliance with antithyroid medication checked and FBC and thyroid function (TSH, FT4, FT3 and TRAb) will be assessed. Other assessments include goitre size assessment, eye examination, patient-reported quality of life measures (Graves’ Orbitopathy Quality of Life Instrument^4^ and Thyroid Patient-Reported Outcome^19^), specific antibody tests and other safety bloods (FBC, LFT). At the end of their participation in the trial, participants will be asked their opinion on which treatment allocation they received, and if they would recommend their treatment to a friend with the same condition. In addition, we plan to undertake exploratory analyses of lymphocyte subsets determined by flow cytometry and transcriptomic markers of plasma cells using quantitative reverse transcription-PCR.^20^

**Table 4 T4:** *S*chedule of assessments

Assessment/activity	Visit 1	Visits 2 & 3	Visit 4	Visit 5	Visit 6	Visit 7	Visit 8	Visit 9
			Day 0	Day 14 (±3 days)	4 weeks (±1 week)	6 weeks (±1 week)	12 weeks (±1 week)	24 weeks (±1 week)
Written informed consent	X							
Demographics & medical history	X							
Physical examination	X							
12-lead ECG	X							
Eye examination (CAS)	X							
Hepatitis B & C serology, HIV	X							
Bone chemistry	X							
Coombs, blood group, RBC phenotyping	X							
Pregnancy testing (females)	X						X	
COVID-19 vaccination offered		X X						
IMP infusion			X	X				
Weight	X	X	X	X	X	X	X	X
Resting pulse rate	X		X	X	X	X	X	X
Goitre size assessment	X		X			X	X	X
FBC	X		X	X	X	X	X	X
TSH, FT4, FT3, TRAb	X		X	X	X	X	X	X
U&E, LFT	X		X	X	X	X		
IgGAM	X		X			X	X	X
Height			X					
Eye examination (composite eye index)			X			X	X	X
Thyroid volume on USS			X					X
QoL questionnaires (GOQoL, ThyPRO)			X			X	X	X
TgAb, ATPO			X			X	X	X
Specific antibodies			X				X	X
Exploratory analysis sample			X			X	X	X
Vital signs			X	X				
Compliance with ATD			X	X	X	X	X	X
Concomitant medication		X	X	X	X	X	X	X
Adverse event reporting		X	X	X	X	X	X	X
Follow-up phone call			X	X				
End of trial questions								X

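### Hepatitis B screening is meant to guard against reactivation of latent virus, but the only assay named is surface antigen, and no liver function test is scheduled after week 6

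*Protocol article*

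**What the plan says.** The Risk assessment section gives the purpose of the viral screen: "There is a potential for reactivation of latent viral illness, and so all participants will be screened for hepatitis B, C and HIV infection". The same sentence adds that "participants with previous shingles or current untreated cervical dysplasia will be excluded". The Exclusion criteria list "Previous shingles, known untreated cervical dysplasia, hepatitis B and C or HIV infection", without naming an assay or limiting hepatitis B to current infection.

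The section on patient identification, consent and screening itemises the eligibility blood tests. Its viral part reads "hepatitis B surface antigen, hepatitis C virus antibodies, HIV". Hepatitis B core antibody and HBV DNA are not mentioned anywhere in the article. Table 4 has one row for hepatitis and HIV serology, marked at Visit 1 only, with no assay named.

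The Table 4 row for urea, electrolytes and LFT is marked at Visit 1, day 0, day 14, week 4 and week 6, and is blank at weeks 12 and 24. The Assessments text counts LFT among the safety bloods but gives no visit times. Under Trial design, patients in both stages "will be followed up for 24 weeks". The Intervention section states: "After the day 14 visit, no further IMP will be administered".

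**The concern.** The stated hazard is reactivation of latent virus, and the named test covers only part of it. Surface antigen finds people who are currently infected. It does not reliably find people with past or occult infection who are surface-antigen negative, and such infection can reactivate under immune-depleting treatment. The article does not say this; it is general medical knowledge.

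If the panel is applied as written, a participant with unrecognised surface-antigen-negative hepatitis B would pass this test and could receive daratumumab. If the virus then reactivated after week 6, no scheduled test would show liver injury. The bloods marked at weeks 12 and 24 (blood count, thyroid tests, immunoglobulins, thyroid autoantibodies and specific antibodies) are not liver tests.

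The plan itself expects antibody effects to matter late. Specific antibodies are measured at weeks 12 and 24, and the Risk assessment section provides for revaccination if immunity has been lost by the end of the study. Scheduled liver monitoring stops well before that. What is at stake is participant safety.

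**Working it through.** No sample size, power or type I error figure bears on this point, and the plan states no figure to reproduce. The check compares the sections and counts time in the visit schedule.

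**Purpose against test**
- Purpose (Risk assessment): reactivation of latent virus.
- Test (screening blood list): surface antigen only.
- Covered: current infection, including chronic carriers.
- Not covered: surface-antigen-negative past or occult infection, unless it is already known and picked up by the medical history or the exclusion criterion.

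**Reading Table 4**
- The table has eight visit columns: Visit 1, Visits 2 and 3, day 0, day 14, and weeks 4, 6, 12 and 24.
- Urea, electrolytes and LFT row: X, blank, X, X, X, X, blank, blank.
- Full blood count row: X, blank, then six X. It fills every column from day 0, which confirms the alignment. The two final blanks in the LFT row therefore belong to weeks 12 and 24.

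**Length of the interval without a scheduled LFT**
- Nominal: 24 − 6 = 18 weeks, and 18/24 = 75% of follow-up.
- With the ±1 week visit windows: shortest 23 − 7 = 16 weeks, longest 25 − 5 = 20 weeks.
- From the second infusion (day 14): week 6 is day 42, so LFT cover lasts 42 − 14 = 28 days. Week 24 is day 168, so follow-up lasts 168 − 14 = 154 days. The remainder is 154 − 28 = 126 days, and 126/154 = 82%.
- Using both windows (day 14 ± 3 days, week 6 ± 7 days), the last scheduled LFT falls between 35 − 17 = 18 and 49 − 11 = 38 days after the second infusion.

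**Who can still benefit**
- The article gives "planned end of trial (last patient last visit): April 2024", and Trial status says stage 2 has begun.
- Week 24 is 168 days after day 0. Counting back from 1 April 2024 gives 16 October 2023; from 30 April 2024 it gives 14 November 2023 (each ±1 week for the visit window). The last first infusion is planned for about then.
- A change to screening reaches only stage 2 participants not yet dosed. Stage 2 has 15 planned patients. With equal allocation, 15 × 1/2 = 7.5 (one dose plus placebo) to 15 × 2/3 = 10 (two doses plus placebo) would receive active drug, and fewer than that remain untreated. The exact number is not given.
- LFTs added at weeks 12 and 24 also reach treated participants who have not yet had those visits.

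**The case against.** The strongest reply is that the article is consistent with itself. It excludes hepatitis B infection, says participants will be screened for infection, and names a test that detects infection. A reader might infer that the screening list contradicts the exclusion criterion, or that carriers would be let in. Neither follows. Surface antigen finds carriers, and known past infection can be caught by medical history. The shortfall appears only when one adds the outside fact that surface-antigen-negative infection can reactivate.

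A reader might also see the exclusion of previous shingles as proof that the plan treats two latent viruses differently. The documents do not support that. Previous shingles is a past illness found by history, and no varicella serology is listed, so silent carriage of that virus is not sought either.

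The article condenses protocol V.6.0, which may name more assays, and Table 4's word for the hepatitis tests is broader than surface antigen. This lowers confidence about the panel but does not remove the point: the screening section itemises its tests down to red cell phenotyping and names one specific hepatitis B marker, and the two LFT cells in a printed visit-by-visit schedule are blank.

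Finally, 75% and 82% are shares of follow-up time, not risks. They apply to every participant, whereas the harm concerns only someone with unrecognised infection who receives active drug, given as two infusions in a 30-patient trial. Adverse event checks continue at weeks 12 and 24, and the Risk assessment section promises regular blood monitoring, though it names no liver test and makes the promise while discussing background thyroid treatment. Unscheduled LFTs remain possible. All of this stands and limits the priority of the point.

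**Conclusion.** The point holds as a safety improvement of low to moderate priority. The reason given for screening is wider than the one hepatitis B assay named, and scheduled liver testing stops at week 6 of a 24-week follow-up, leaving 18 weeks (16 to 20 within visit windows) uncovered although blood is drawn twice in that time.

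The size of the risk cannot be stated: the article gives neither a prevalence of surface-antigen-negative hepatitis B nor a reactivation rate. It would be wrong to conclude that any participant has been harmed, or that the schedule percentages measure the chance of harm. The efficacy analysis and sample size are unaffected.

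The conclusion rests on three assumptions: that the itemised screening list and Table 4 reflect what is done, that surface-antigen-negative infection can reactivate (general medical knowledge), and that some stage 2 participants are still undosed or in follow-up. The third affects only the reach of the changes.

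**What to change.** Make two separate changes.

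1. **Screening.** Add hepatitis B core antibody to the Visit 1 blood tests for participants not yet dosed, and state what a positive result leads to: either exclusion, or HBV DNA testing with continued monitoring. If protocol V.6.0 already specifies a wider panel, only the wording of the screening list needs correcting.
2. **Monitoring.** Mark LFT at the existing week 12 and week 24 visits for all participants, including those already treated. This should not depend on the core antibody result. Otherwise, participants who passed Visit 1 before the change would gain nothing, and the gap would remain for everyone else. It stands on its own whatever the full protocol says about the screening panel.

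The cost is one extra assay on a sample already drawn at Visit 1, an occasional screen failure, HBV DNA tests for any core-antibody-positive participants who are kept, LFTs on blood already taken at two visits, and a protocol amendment.

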### Randomisation

Randomisation will be performed by delegated and trained members of the site research team using the online system ‘Sealed Envelope’—a central, secure, 24-hour web-based randomisation system. In both stages, the allocation sequence will be computer generated using a random permuted block design. Patients will be randomly allocated equally to the available daratumumab doses or to a matched placebo; for example, if two doses of daratumumab plus placebo are to be used, the allocation would be 1:1:1. There are no stratification factors.

In stage 1, patients will be allocated to receive a dose of daratumumab (9, 3, 1, 0.5 mg/kg) or matched placebo. In stage 2, patients will be allocated to receive daratumumab (one or two dose levels as determined by the interim analysis) or matched placebo.

### Intervention

Each participant will receive two infusions, on day 0 and day 14 (±3 days). The prescribed daratumumab dose will be prepared in a 500 or 1000 mL bag of sodium chloride 0.9%, using the most recent available participant weight to calculate banded dose (see table 2 for volume and infusion rate). Each participant will be prescribed the same banded dose for both infusions, using the same weight for both. Where placebo is allocated, a volume-matched bag of sodium chloride 0.9% will be used. All participants will be pre-medicated with three non-IMPs, paracetamol (1 g orally), methylprednisolone (100 mg intravenously) and chlorphenamine (10 mg intravenously) at least 30 min prior to their allocated infusion.

**Table 2 T2:** Infusion rate table

Time (hour:min)	Rate (mL/hour)	Total volume at end of time (mL)
Stage 1 (1000 mL)		
1	80	80
2	160	240
3	240	480
4	320	800
4:40	320	1000
Stage 2 rate A (1000 mL)		
1	50	50
2	100	150
3	150	300
4	200	500
5	200	700
6	200	900
6:30	200	1000
Stage 2 rate B (500 mL)		
1	50	50
2	100	150
3	150	300
4	200	500

The maximum infusion rate of daratumumab was determined by the recommendation of the SmPC for daratumumab (DARZALEX 20 mg/mL concentrate for solution for infusion). For stage 1, all participants will receive the IMP/placebo diluted in 1000 mL sodium chloride 0.9% for both infusions. For stage 2, some patients may receive higher doses of daratumumab, so a more prolonged first infusion will be given to all participants. If participants have no IRRs during their first dose in stage 2, then the second dose may be given in 500 mL sodium chloride 0.9% with a faster infusion rate, in line with SmPC recommendations.

IMP, investigational medicinal product; IRRs, infusion-related reactions; SmPC, Summary of Product Characteristics.

Vital signs (pulse rate, blood pressure and temperature) will be recorded prior to the start of each infusion and every 15 min during the course of the infusion, and for 1 hour afterwards. Infusion-related reactions will be addressed as shown in table 3, and documented as an AE. Infusion charts will be completed to document compliance with prescribed dose. Participants will be followed up by phone approximately 2 days after each infusion visit to check for any AEs. After the day 14 visit, no further IMP will be administered. Patients will continue their regular medications, including antithyroid drugs and beta-blockers throughout the study, as deemed appropriate by the clinical team.

**Table 3 T3:** Infusion-related reactions (IRRs)

Grade 4 reactions	Life-threatening	Stop and permanently discontinue infusion.
Grade 3 reactions	Severe, including: Tachycardia ≥120 BPM or drop in SBP ≥30 mm Hg over pre-infusion with symptoms Rise in SBP ≥30 mm Hg over pre-infusion or tachypnoea ≥24/min Hypoxia SaO_2_ <92%	Stop infusion until observations improve and restart at 50% of the infusion rate at which IRR occurred. If the patient does not experience additional symptoms, infusion rate escalation may be resumed at increments and intervals as appropriate. The procedure above should be repeated in the event of recurrence of grade 3 symptoms. After the infusion restart attempts, the IMP treatment will be permanently discontinued upon the third occurrence of a grade 3 or greater IRR.
Grade 1–2 reactions	Mild to moderate, including: nasal congestion cough chills throat irritation vomiting nausea	Stop infusion in case of clinically significant reaction only until observations improve and restart at 50% of the infusion rate at which IRR occurred. If the patient does not experience any further IRR symptoms, infusion rate escalation may be resumed at increments and intervals as clinically appropriate up to the maximum rate. Infusion does not need to be stopped if IRR is not clinically significant.

BPM, beats per minute; IMP, investigational medicinal product; SaO_2_, arterial oxygen saturation; SBP, systolic blood pressure.

